## Abstract

**Background:**

Deviation from the physiological glucocorticoid dynamics (circadian and underlying ultradian rhythmicity) is a common characteristic of various neuropsychiatric and endocrine disorders as well as glucocorticoid-based therapeutics. These states may be accompanied by neuropsychiatric symptomatology, suggesting continuous dynamic glucocorticoid equilibrium is essential for brain homeostasis.

**Methods/design:**

The study consists of two parts. The preliminary stage of the study aims to validate (technically and pharmacologically) and optimise three different patterns of systemic cortisol administration in man. These patterns are based on the combinatory administration of metyrapone, to suppress endogenous cortisol production, and concurrent hydrocortisone replacement. The second, subsequent, core part of the study is a randomised, double-blinded, placebo-controlled, crossover study, where participants (healthy male individuals aged 18–60 years) will undergo all three hydrocortisone replacement schemes. During these infusion regimes, we plan a number of neurobehavioural tests and imaging of the brain to assess neural processing, emotional reactivity and perception, mood and self-perceived well-being. The psychological tests include: ecological momentary assessment, P1vital Oxford Emotional Test Battery and Emotional Potentiated Startle Test, Leeds Sleep Evaluation Questionnaire and the visual working memory task (n-back). The neuroimaging protocol combines magnetic resonance sequences that capture data related to the functional and perfusion status of the brain.

**Discussion:**

Results of this clinical trial are designed to evaluate the impact (with possible mechanistic insights) of different patterns of daily glucocorticoid dynamics on neural processing and reactivity related to emotional perception and mood. This evidence should contribute to the optimisation of the clinical application of glucocorticoid-based therapeutics.

**Trial registration:**

UK Clinical Research Network, IRAS Ref: 106181, UKCRN-ID-15236 (23 October 2013)

## Background

### Glucocorticoid dynamics and neurobehavioural equilibrium

The hypothalamic–pituitary–adrenal (HPA) axis is a complex homeostatic system, consisting of multiple feedforward and feedback regulatory interactions from the corticolimbic areas of the brain to the adrenal cortex [1]. These interactions result in both a circadian and an ultradian rhythm of cortisol secretion [2], which may be further modified by internal or external stressors [3].

HPA activity can be classified within two categories: (i) the regulation of internal homeostatic mechanisms (many of which have a circadian pattern) and (ii) the coordination of stress responses. Although there are glucocorticoid receptors in almost every tissue of the body, these hormones’ predominant effects relate to metabolic, immunological or cognitive functions. The wide spectrum of glucocorticoid-related biological actions has been exploited in the field of therapeutics for various disorders, though long-term use and/or high doses have been accompanied by numerous side effects [4].

Glucocorticoids modify the physiology of the central and peripheral nervous system at multiple levels. They interfere with the molecular processes involved in the modulation of the neuroinflammatory response, neurodegeneration and neuroregeneration/neurogenesis, neuronal viability and the cellular metabolic balance of neuronal and glial populations during developmental stages. Moreover, glucocorticoids regulate the state of activity of most systems of neurotransmission and synaptic plasticity, especially under acute stressful conditions or during chronic post-stress cognitive adaptations. Ultimately, glucocorticoids modify the status of emotional reactivity, cognitive precision and overall behaviour [1].

Glucocorticoid-dependent signalling has been associated with a number of neurological (stroke, traumatic brain injury, neurodegenerative disorders) and psychiatric disorders (depression, psychosis, post-traumatic stress disorders, antisocial behaviour, anxiety disorders and addiction). Similar problems, mainly fatigue, depression or dementia, seem to arise in patients whose treatment strategy involves high dose and/or long-term use of glucocorticoid-related therapeutics (even in cases of substitution therapy), as well as in patients with endogenous hypersecretion (Cushing’s syndrome) or deficiency (Addison’s disease, congenital adrenal hyperplasia) of glucocorticoids [4].

In all of these conditions there is a deviation from physiological glucocorticoid dynamics. The rationale for this protocol is therefore to examine whether glucocorticoid rhythmicity differentially regulates neural processing related to mood and emotional perception. These are cognitive aspects controlled via the corticolimbic areas of the brain and are susceptible to glucocorticoid effects.

### Aims of this paper

This article serves the following purposes: (1) the presentation of the study protocol and the underlying scientific evidence that led to its specific design, (2) the development of a metyrapone and hydrocortisone block and replace regime that allowed precise pharmacological manipulation of the underlying glucocorticoid rhythm, (3) the presentation of the temporal design of our magnetic resonance imaging (MRI) protocol and some technical aspects on approaching neuroimaging analysis, following the guidelines for reporting functional neuroimaging data.

### Rationale of the study

The importance of the glucocorticoid circadian rhythm in maintaining homeostasis has been long recognised. Nevertheless, there is little evidence available concerning the clinical impact of the underlying physiological ultradian (pulsatile) rhythm.

Preclinical research work over the last decade has highlighted the importance of ultradian pulses, which are synchronised between the blood, subcutaneous tissue and the brain [5], and lead to rapid and transient activation of its target receptors, resulting in dynamic genomic, neuroendocrinological and behavioural changes [6]. Moreover, they differentially affect neuronal plasticity and neurotransmission [7].

A number of clinical trials in healthy subjects, using functional neuroimaging techniques, have added valuable insights into the influence that glucocorticoids exert on cognitive and behavioural functions. Under such experimental settings, it has been shown that hydrocortisone administration imposes changes in emotional processing, attention or working memory related to either alterations in corticolimbic activity or differential functional connectivity [8–10]. Nevertheless, none of these clinical trials investigated the relevance of pattern administration (that is, the relevance of altered glucocorticoid rhythmicity) to these neurobehavioural changes. The focus was to contrast the state of high, stress-related glucocorticoid concentrations to the normal, non-stress levels, and study either the rapid (mediated by the activation of the membrane-associated glucocorticoid receptors) and/or the delayed (mediated by the activation of the nuclear glucocorticoid receptors) glucocorticoid effects on cognitive performance and emotional perception.

### Main research questions and hypothesis

Our research team has adopted a novel approach, which enables us to infuse replacement steroids in either a physiological circadian rhythm with its underlying ultradian rhythm or as a constant infusion, which abolishes the ultradian component of the circadian rhythm. This will allow us to test our hypothesis that the pattern of systemic glucocorticoid fluctuations leads to differential neurobehavioural phenotypes and activation of brain areas related to mood and emotional processing.

## Methods

### Overview of the study design

This is a physiological, pilot study on healthy, adult male volunteers, who will undergo three different strategies of hydrocortisone replacement after their endogenous glucocorticoid production is pharmacologically suppressed in a safe and reversible manner. The study has two stages: a preliminary stage (stage 1), where the pharmacological interventions are optimised and biochemically validated (presented here). The second stage of the study (stage 2) will be a double-blinded, placebo-controlled, three-way crossover, neurobehavioural study, in which healthy male subjects randomly alternate the three different modes of hydrocortisone replacement. The effect of each condition is assessed using functional and perfusion imaging of the brain and a series of psychological measurements assessing emotional reactivity and self-perceived well-being. For both study parts, the same regulations apply in terms of inclusion and exclusion criteria, the recruitment process and biomedical ethics. In the second stage of the study some additional inclusion and exclusion criteria, as well as steps in the recruitment process, will be applied (as discussed below).

### Inclusion and exclusion criteria

We shall recruit healthy volunteers, with no medical history and a normal physical examination assessed during the screening process by a qualified physician. Volunteers must not be casual smokers or consume excessive amounts of alcohol frequently, and additionally, they must not consume excessive amounts of caffeinated drinks (for details refer to Table 1). Since there are age-, gender- and working routine-specific factors that affect the mode of HPA axis function [11], this study is limited to male individuals, aged between 18–60 years old, who are not shift workers [12]. Furthermore, volunteers are excluded if they have participated in any other drug trial within the last two months prior to current study participation or have used any medication (prescribed, over the counter or recreational), including topical steroids and inhalers, within 48 hours of the current study initiation.

**Table 1 Tab1:** Exclusion criteria of the study

1. Non-healthy individuals
• Previous medical history for any chronic condition in the last three months, active disease, or abnormal physical examination as verified by a qualified physician.
2. Casual smoking
• >6 cigarettes per day.
3. Frequent, heavy alcohol consumption
• >21 units/week.
4. Frequent, heavy caffeine consumption
• >4 caffeinated drinks/day.
5. Gender: female
6. Age: < 18 and > 60 years old
7. Shift workers
8. Participation in an investigational drug trial within the past two months
9. Intake of any medication (prescribed, over the counter or recreational) including topical steroids and inhalers, within 48 hours of the study initiation
• Urine sampling for testing for drugs of abuse^a^
Stage 1 (pharmacological validation) only
10. Needle phobia
Stage 2 (neurobehavioural investigation) only
11. Left-handed or ambidextrous
• Tested with the Edinburgh Handedness Inventory [13]
12. Dyslexia
13. Claustrophobia
14. Contraindication to MRI scan
15. Non English-language users

^a^Urine sampling for testing for drugs of abuse takes place during the recruitment process. In addition, during study stage 2 (neurobehavioural investigation), urine sampling is repeated prior to starting the trial on day 1 of each of the three study arms, as well as prior to the scanning session on day 5 on each of the three study arms. A seven-drug (multi-panel) dip and read immunoassay is being used, offering high accuracy in detecting cocaine, amphetamine, methamphetamine, tetrahydrocannabinol (cannabis), opiates, barbiturates and benzodiazepines (SureScreen Diagnostics®)

Needle phobia was an additional exclusion criterion during recruitment for stage 1, as 24-hour blood sampling via a cannula is required. For stage 2, volunteers need to be non-dyslexic, right-handed [13] and fluent in the English language, to ensure they can respond to various verbal stimuli included in the behavioural test and/or questionnaires. Participants also need to pass MRI safety screening and must be able to tolerate spending more than one hour inside the MRI scanner bore. Table 1 gives detailed information about the exclusion criteria.

### Recruitment process

For both studies the same recruitment methods have been used. Study adverts briefly describe the scope of the investigation and basic inclusion/exclusion criteria. Posters are being displayed across multiple faculties within the University of Bristol. Electronic adverts are being sent to subjects who have expressed interest in our studies in the past and given permission to be contacted about study opportunities in the future. The study is also publicly advertised on the University of Bristol Department of Psychology webpages, and is included in the monthly newsletter sent to all subscribers of the Psychology mailing list interested in human research (subscription is free to all members of the general public). Advertisement for study stage 2 occurs after completion of stage 1, allowing for optimised treatment schemes (see below) and temporal design of the neurobehavioural investigation.

Figures 1 and 2 summarise the study recruitment procedures for both stages of the study. Standard recruitment procedures are used for both stages of the study. Interested volunteers may contact the research team via a secure University email address or telephone number. If the information provided suggests no reason for initial exclusion, subjects are sent the participant information sheet (PIS). The PIS details the aims/scope of the study in lay language, all clinical and experimental procedures involved, the ethical framework which governs the study, the volunteers’ responsibilities and the healthcare and safety information. After receiving the PIS, participants have up to six weeks to consider the information and decide if they would like to take part. If interested, participants are requested to contact the study team by phone or email. Study investigators can also contact potential participants after four weeks if no reply has been received. All interested participants are initially asked to take part in a short screening phone call, arranged at a convenient time. Phone screening allows initial assessment of eligibility and a chance for the investigator to ensure participants have read and understood the PIS and what would be involved in the study. Participants are also encouraged to ask any questions they may have.

**Fig. 1 Fig1:**
[figure not shown]
Main steps followed in recruiting and working with volunteers during study stage 1. Interested participants were phone screened, and if screening was positive, an initial appointment was scheduled to discuss in full detail the parameters of the study and answer any queries. During that appointment, a full screening process takes place. If participants are still eligible and willing to participate, signed informed consent is obtained. A date to conduct the five-day interventional study (metyrapone and hydrocortisone administration) is then arranged. The 24-hour study is performed after midday (around 2:00–3:00 pm) of day 4 until after midday (around 2:00–3:00 pm) of day 5. HABS: human automated blood sampler

**Fig. 2 Fig2:**
[figure not shown]
Main steps followed in recruiting and working with volunteers during study stage 2. Interested participants are phone screened, and if screening positive, an initial appointment is scheduled to discuss in full detail the parameters of the study and answer any queries. During that appointment, a detailed screening process would take place. If participants are still eligible and willing to participate, signed informed consent is obtained. Additionally, as part of the screening process, participants need to give a urine sample to test for drugs of abuse and undergo an initial anatomical magnetic resonance (MR) scan. If still eligible, the dates for the conduction of the three study arms are arranged. The order of treatment arm allocation is random and unknown to the volunteers and the study investigators. This is determined by an external authority and takes place prior to the start of arm 1. Interventions during the three study arms were designed and validated during the previous study stage. Each of the three arms takes place with a temporal distance from the previous one of at least two weeks (*). EMA: ecological momentary assessment, ETB: emotional test battery, EPST: emotion potentiated startle test, LD: last study day, LSEQ: Leeds Sleep Evaluation Questionnaire, MRI: magnetic resonance imaging, RAP: randomisation phase, WP: wash-out period

If participants are happy to continue and found eligible at this stage, they are invited to attend a more detailed screening visit. During that appointment, a detailed, formal screening process takes place (including the acquisition of a medical history and a physical examination), all the procedures and the scientific background/justification and any medical issues related to the study are discussed and explained in detail. Participants are again encouraged to raise any concerns or queries, and if still willing to take part in the study, they are asked to sign the relevant written consent forms.

Screening for study stage 2 also involves ensuring the participant is suitable for MRI scanning; this is undertaken by using specific screening forms. If it is safe to scan the participant, an additional visit is booked for a preliminary MRI examination during which a high-resolution, anatomical MRI scan is acquired. This initial MRI scan serves two purposes: (1) acquiring the data necessary for subsequent registration of low-resolution functional fMRI data to a “standard” MRI template for neuroanatomical localisation of obtained functional imaging data, and (2) assessing the ability of the subject to lie still inside the MRI scanner bore for long periods. Prior to the scan, participants are also asked to produce a urine sample to test for drugs of abuse (see Table 1).

### Medical issues, quality control, bioethics and trial monitoring

Local ethical and institutional approval has been obtained. The study was discussed with the Medicines and Healthcare products Regulatory Authority (MHRA) and formal approval was deemed unnecessary. The study is conducted according to the principles of the Research Governance Framework for Health and Social Care and the international conference for harmonisation of good clinical practice (ICH GCP, declaration of Helsinki). The study is being performed subject to the Faculty of Science Human Research Ethics Committee of the University of Bristol (REC, ethics approval code: 2706132525) and local Research and Development (R&D) approval of the University Hospitals Bristol (UHB, National Health System Foundation Trust) (reference code: ME/2013/4325). The study is monitored and audited in accordance with the R&D governance procedures of UHB and the University of Bristol. Case record forms are produced, and these and all study-related documents will be made available on request for monitoring and audit by the Trust, University and REC.

Study-related information and informed consent is administered by the investigators. Participants receive information designed to inform them extensively on the topic of the investigation. This includes information regarding the overall study, its goals, methods, health and safety issues and procedures involved. They also receive a detailed presentation of the MRI techniques, their limitations and their safety issues. In addition, during the initial appointment (see above), investigators ensure that participants’ questions and concerns are addressed and fully answered. Participants are informed that they have the right to discontinue their participation at will, at any time without giving a specific reason. Lastly, participants are encouraged to contact the research team at any later point if they feel they require further elaboration on a study-specific topic. Afterwards, eligible male volunteers who are still interested in participating in the study are requested to read and sign a consent form acknowledging the principles outlined above.

The possible presence of unwanted effects due to the pharmacological intervention or other medical processes during the study has been taken into consideration, and all necessary measures, ensuring participants’ safety, have been implemented. For instance, side effects of metyrapone include nausea, vomiting, drowsiness, abdominal pain and allergic skin reactions. For this reason, volunteers are explicitly instructed to accompany pills with food intake to avoid/attenuate gastrointestinal discomfort. If side effects develop, participants are strongly advised to contact the research team, so the metyrapone dose can be decreased for 24 hours and increased again, symptoms allowing.

Potential side effects of (high doses of) hydrocortisone include problems with disturbed sleeping, abdominal pain and heartburn. Since all volunteers will be receiving a cortisol blocking agent (metyrapone) in combination with adequate hydrocortisone replacement therapy, there should be no issues with symptoms related to hypoadrenalism or cortisol excess. For safety reasons, the risks and symptoms of a hypoadrenal crisis are explicitly discussed with participants, as well as what they need to do should they become unwell at all during the study [14]. An emergency box is given to all participants for the duration of their study sessions, containing hydrocortisone for intramuscular and per os administration, as well as other equipment related to the pump handling and subcutaneous delivery. Moreover, all participants have an emergency card to keep on their person at all times with details of study drugs and out-of-hours contact information (24-hour emergency telephone number).

There is a rare possibility of an anaphylactic reaction [15] to parenteral hydrocortisone succinate administration in a subject with no prior history of anaphylaxis. All medical and biomedical procedures related to this study will occur in the Joint Clinical Research unit at UHB or the Clinical Research and Imaging Centre of the University of Bristol (CRICBristol). Both units’ basic resuscitation equipment has been inspected and agreed to be appropriate by the UHB resuscitation officer, and there is immediate access to the full resuscitation team if they are needed. A standard operating procedure and risk assessment for the procedure includes clear instructions regarding the presentation and initial management of anaphylaxis.

In case of technical, pump-related and drug delivery-related issues, such as subcutaneous pump line falling out/accidental removal, all participants are taught how to perform a line change (materials provided in the emergency box) and instructed to contact a study researcher (24-hour emergency telephone number provided) so that the pump can be checked and a replacement emergency kit provided. In case of a pump failure/malfunction, subjects are instructed to contact a study researcher. If a replacement pump cannot be provided within 3 hours, the subject will be asked to take oral hydrocortisone replacement (provided in the emergency box).

Other minor unwanted effects that may occur during the study are discomfort, bruising, infection or allergic reaction at site of insertion of infusion pump/cannula, vasovagal reaction or bruising due to intravenous cannulation (during the preliminary stage of the study), and a feeling of claustrophobia during MRI scanning (during the core part of the study). Adverse events will be recorded in accordance with the ICH GCP and the UHB’s research-related adverse event reporting policy. The study will be stopped prematurely in the case of significant adverse events.

Concerning the MRI scans, the subjects are made aware that these scans are not diagnostic and will be interpreted solely for the purposes of the study. Nevertheless, study researchers do have a duty of care. As a consensus between these two principles, this study has adopted the guidelines provided by Illes et al. [16], which explain the procedures for dealing with incidental findings in brain imaging research. Based on these guidelines, our scanning protocol (see below) contains the minimum required sequences for research and does not include extra scans for diagnostic purposes. All scans are reviewed by a clinically qualified (non-radiologist) member of the research team. If any concerns are noted, the images will be sent for consultation and/or referral to a radiologist for clinical evaluation. After assessment the qualified radiologist will report any incidental findings to the lead researcher and provide guidance on what should be conveyed to the participant’s primary care provider (this information is collected at screening). After reporting, the responsibility for assessing the importance of the findings and acting on them rests with the primary care provider.

Volunteers are free to withdraw from the study at any time. Should a subject withdraw from the study, another will be recruited in his/her place. It is not anticipated that withdrawn volunteers will require any follow-up.

With regards to a randomisation and/or blinding code break during the second stage of the study, a copy of the codes will be kept in the Bristol Royal Infirmary University Hospital Pharmacy and in the site file. The codes may only be broken under the following conditions with the agreement of the chief investigator and REC except under the case of an emergency: (i) it is deemed clinically necessary (for example, treatment of an adverse event is dependent upon knowledge of the drug administered), (ii) the study must be terminated for safety reasons, or (iii) a third party requires the information (for example, a coroner).

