All visits take place in the Joint Clinical Research unit (UHB). On day 1 participants are fitted with the subcutaneous pump and are given precise instruction on how to receive their oral medication. On day 3 participants wearing either of the pumps attend the unit for a pump syringe and line change. On day 5, the 24-hour blood sampling study is undertaken, using the human automated blood sampler (HABS). Blood samples are collected via an intravenous cannula every one hour for serum corticotrophin (ACTH) and cortisol concentration estimation. For those receiving hydrocortisone via the subcutaneous pulsatile pump, cortisol was being estimated every 10 minutes, since we anticipated that cortisol would fluctuate in a more dynamic manner (approximating its normal, ultradian rhythm). During the 24-hour sampling procedure, participants give approximately half a pint of blood (half the amount of blood taken at blood donation). All blood is replaced with an equal volume of normal saline.

During the blood sampling period, participants are served a hot meal at 7:00 pm, breakfast at 07:00 am and lunch at 12:30 pm. Refreshments are offered between meal times and recorded. Participants are asked to go to sleep at 11:00 pm when the lights are switched off. During the lights-on period, participants are allowed to work, read, watch films or relax. A member of staff is present in a room adjacent to the experimental room to monitor them at all times. At the end of the study (in the early afternoon), when the intervention is terminated, participants are instructed to take orally 5 mg of hydrocortisone during dinner to ensure proper cortisol replacement for that day. This ensures there has been adequate time for the metyrapone to have cleared and resumption of endogenous cortisol production. Participants are called the following day to check that there have been no adverse events and note any issues they wish to report.

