On day 3 participants attend the hospital for a pump syringe and pump line change, while the investigator also monitors individuals’ compliance to the treatment scheme (counting the number of remaining pills) and to answering the study phone’s questions. Finally, on day 5 participants attend CRICBristol where they undergo MRI scanning, complete a sleep questionnaire and undertake a series of behavioural tests (see below). At the end of the study visit, participants return all study material (android phone, remaining pills), are disconnected from the pump and are instructed to take 5 mg of hydrocortisone orally during lunch and again during dinner to ensure proper cortisol replacement for the remaining day. This ensures there has been adequate time for the metyrapone to have cleared and resumption of endogenous cortisol production. They will then receive a follow-up phone call the following day to check to see how they are feeling and if they have any issues they wish to report.

Compliance to the treatment protocol is encouraged by (1) giving participants at arm day 1 a detailed, written five-day timetable, with instructions on the timings and the number of metyrapone and hydrocortisone/placebo pills they need to take, (2) counting the remaining pills at arm days 3 and 5 to verify that they are consumed in the proper quantity, and (3) prompting the participants at arm day 3 to accurately follow their treatment scheme and to constantly wear the pump. Furthermore, compliance to the oral treatment protocol is also supported via three reminder messages (in the morning, at 1:00 pm and at 7:00 pm) delivered every day through the study phones carried by each subject.

### Assessments during study stage 2

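### The statement that withdrawn volunteers need no follow-up does not separate wash-out from metyrapone dosing, and it is at odds with the next-day call made after every planned end of treatment

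*Protocol article*

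**What the plan says.** The section on medical issues, quality control, bioethics and trial monitoring sets the withdrawal rule: "Volunteers are free to withdraw from the study at any time". A withdrawn volunteer is replaced by a new recruit, and then: "It is not anticipated that withdrawn volunteers will require any follow-up". The rule covers both stages and does not depend on when the man leaves.

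The planned end of treatment is handled differently.

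- **Stage 1.** Participants take 5 mg of oral hydrocortisone at dinner. The section on stage 1 adds: "Participants are called the following day to check that there have been no adverse events".
- **Stage 2.** At the end of each arm they are "instructed to take 5 mg of hydrocortisone orally during lunch and again during dinner to ensure proper cortisol replacement for the remaining day". The reason follows: "This ensures there has been adequate time for the metyrapone to have cleared and resumption of endogenous cortisol production". Then comes the call: "They will then receive a follow-up phone call the following day to check to see how they are feeling".

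The general safeguards are a briefing on hypoadrenal crisis, an emergency card, a 24-hour telephone number and an emergency box: "An emergency box is given to all participants for the duration of their study sessions, containing hydrocortisone for intramuscular and per os administration". For a failed pump there is a specific rule: "If a replacement pump cannot be provided within 3 hours, the subject will be asked to take oral hydrocortisone replacement".

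**The concern.** The plan's reason for care after an arm is recent metyrapone exposure, not completion of the arm. A man who stops on day 3 or day 4 has that exposure too. Read as written, the plan calls the man who finishes and anticipates no contact with the man who leaves part-way.

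The man who leaves part-way may be the one more likely to be unwell. Nausea and vomiting are listed as metyrapone effects, and they are plausible reasons to stop. In stage 2 he takes tablets and wears a pump, one of which is placebo, so he does not know which of the two has been supplying his hydrocortisone.

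Two things are at stake: advice on replacement while endogenous production recovers, and the recording of an adverse event that begins after withdrawal and that the volunteer does not report himself.

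**Working it through.** The plan states no figure on this point, so the check is a comparison of the procedures in the protocol article.

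| Situation | Recent metyrapone? | Bridging hydrocortisone stated | Contact by the team stated |
|---|---|---|---|
| Planned end, stage 1 | Yes | 5 mg at dinner | Call next day |
| Planned end of an arm, stage 2 | Yes | 5 mg at lunch and 5 mg at dinner | Call next day |
| Withdrawal in the wash-out (at least two weeks between arms) | Not after the first days | None stated | None anticipated |
| Withdrawal during metyrapone dosing | Yes | None stated | None anticipated |

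1. **Size of the bridging dose.** In stage 2 it is 5 + 5 = 10 mg, which is 10/20 = 50% of the 20 mg oral daily dose. In stage 1 it is 5 mg, or 5/20 = 25%.

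2. **Wash-out row.** A man who leaves here has normally already had the end-of-arm doses and call. Expecting no further follow-up is reasonable for him, and the sentence fits.

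3. **Mid-arm row.** He has the same recent exposure as the completers in the first two rows, so the stated reason for bridging holds for him as well. The one sentence nevertheless covers him together with the wash-out case.

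4. **The word itself.** The stage 2 text uses the term follow-up for the next-day call. The withdrawal sentence says no follow-up of any kind is anticipated. The two statements therefore meet on the same item, and this is more than a detail left to a fuller document.

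5. **Bridging.** The withdrawal text does not mention it. That is silence, not contradiction.

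6. **Power and analysis.** The power statement refers to 15 participants with complete data, and withdrawn men are replaced. Nothing in the sample size or the primary analysis depends on this sentence.

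**The case against.** The case on the other side is substantial, and most of it stands.

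- **Expectation, not ban.** The sentence says what is anticipated and forbids nothing. It could also have been meant for longer-term follow-up. A reader might infer that contact is ruled out; the text does not say that.
- **Bridging is a stopping procedure.** A reader might infer that the withdrawal text denies bridging doses. It is only silent on them, and a condensed article may leave stopping procedures to the full protocol.
- **Existing safeguards.** Metyrapone was chosen partly for its short half-life. Participants are told to contact the team if side effects develop, are briefed on adrenal crisis, and carry a card with a 24-hour number. Adverse events are recorded under ICH GCP and a hospital policy that is not shown. None of the five stage 1 participants reported side effects. A reader might also infer that the emergency box is taken back on withdrawal; the article does not say so.
- **Tempting numbers.** One could add up the hydrocortisone that Table 3 schedules in the 12 hours after a last metyrapone dose, and set those 12 hours against the 3-hour limit for pump failure. Neither measures harm. Scheduled replacement is not a cortisol deficit, the article gives no clearance time, and the 3 hours is the time allowed to replace a pump for someone still on treatment.
- **The crisis warning in the Discussion.** It concerns a hypothetical metyrapone-only group, not the tail of a last dose after replaced treatment.

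What these arguments do not remove is the different treatment of completers and mid-arm leavers. Completers have the same half-life and the same general safeguards, and the plan still gives them bridging doses and a call. The card and the telephone number also rely on the volunteer to make contact, and no check started by the team is described for a man who leaves during dosing.

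**Conclusion.** The point holds as a minor safety matter. The no-follow-up sentence is worded for all withdrawals, suits those in the wash-out, and is at odds with the next-day call for those who leave during metyrapone dosing. The plan's own reason for bridging applies to these men, but the withdrawal text gives no instruction for them.

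The size is limited. The article gives no withdrawal rate, so the number of men affected cannot be estimated, and no cortisol deficit can be calculated from what it states. Events reported before withdrawal would be recorded; only later events that the volunteer does not report are at risk of being missed.

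The conclusion assumes that follow-up in the withdrawal sentence includes a next-day call, as in the stage 2 text, and that no separate procedure for mid-arm withdrawal in a document not shown already covers the gap. If such a procedure exists, only the wording needs to be aligned.

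**What to change.** Limit the sentence to volunteers who withdraw outside a treatment arm. Add that anyone who withdraws after starting metyrapone in an arm is offered bridging oral hydrocortisone as directed by the study physician, and the same next-day call with adverse events recorded. State that he may decline either without giving a reason. In stage 2 the planned-end doses are the same whatever the arm, so using them as the model needs no code break.

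The cost is a short change to the text and one offered call per mid-arm withdrawal, using a procedure that already exists. The downside is one further offered contact with a volunteer who has chosen to leave.
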